### Blinding

No blinding will take place in this study. Eligible patients who have given informed consent will be randomized into either of the two groups.

### Outcome measures

#### Primary outcomes

Primary outcome of this study is the 28-day all-cause mortality.

#### Secondary outcomes

Secondary outcomes of this study have been seen as follow: 1) The changes of platelets counts (PCs) in the first 7 days; 2) The clinical recovery time of PCs; 3) The amount and proportion of blood transfusion (including platelets, RBC, Frozen plasma); 4) The changes of biomarkers of infection including procalcitonin, C-reactive protein (CRP), endotoxin; 5) The changes of the markers of organ function including cardiac, hepatic, renal, coagulation function; 6) The days free from advanced organ support (including vasoactive drugs/mechanical ventilation/renal replacement therapy) at 28 days; 7) The incidence of bleeding event; 8) The incidences of drug-related adverse events; 9) The length of ICU and hospital stay.

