### Study design and setting

The study is designed as a randomized, open-label, multi-center, controlled study in 5 tertiary academic medical centers which are medical, surgical or general ICUs. [name]. W (Shanghai General Hospital, China) will coordinate all the operational processes and [name]. Y (Shanghai Jiao Tong University School of Medicine, China) will conduct all the statistical analyses. Eligible patients who give their consent to participate in the study will be randomly assigned in a 1:1 ratio to treat with rhTPO (rhTPO group) or without any platelet-elevating drugs (control group). Both two groups receive appropriate medical treatment according to the current guideline of Surviving Sepsis Campaign (SSC) [6], and will be assessed for the outcomes at baseline, after the intervention and at 28-day follow-up. The end of the study is defined by the last follow-up of the last enrolled patient.

Patients in rhTPO group will be treated with rhTPO (TPIAO™, Shenyang Sunshine Pharmaceutical Co., Ltd. Shengyang, China) at a dose of 15000u/d, subcutaneous injection, for 7 consecutive days. RhTPO in the study is for free. The time from randomization to administration of rhTPO will be within 24 h. The drug will be terminated when PCs reach the standard of clinical recovery of platelets (PCs ≥100 × 10^9^/L or the increasing of PCs ≥ 50 × 10^9^/L lasting for at least 3 days) or severe adverse effects happened. The clinical recovery time of platelets was defined as the time it takes to reach clinical recovery. Patients in control group will not be treated with any platelet-elevating drugs.

In both control and rhTPO groups, there is the same standard of platelet transfusion: when PCs are below 10 × 10^9^/L in the absence of apparent bleeding; or below 20 × 10^9^/L if the patient has a significant risk of bleeding; or below 50 × 10^9^/L if the patient has active bleeding or need invasive operation. During the study, any other platelet-elevating drugs will be forbidden.

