Drug-associated serious adverse events should be reported to Shanghai General Hospital within 24 h of participating site study staff becoming aware of the occurrence, and a member of Shanghai General Hospital will be on call 24 h a day via telephone. Serious adverse events are defined as any unexpected medical occurrence that meets one of more of the following criteria: 1) Results in death; 2) Is life-threatening; 3) Results in persistent or significant disability/incapacity. If the patient’s injury is directly induced by rhTPO, the cost of the treatment will be covered by the researchers.

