### Data collection

A case report form (CRF) will be used for all patient who met the enrollment criteria to collect the data. Patients will be followed up to 28 days after randomization. The data will be abstracted from the patients’ electronic medical records: age, ethnicity, gender, patients’ type (medical/surgical), co-comorbidities, sites and pathogens of infection. Then, clinical characteristic baseline and laboratory results were tested within the first 24 h after randomization, including markers of organ functions and biomarkers of infection (Procalcitonin, C-reactive protein, Endotoxin). The severity of disease scores will be recorded, including APACHE II, SOFA, and DIC scores [32] in the first 24 h. The basic serum TPO level in patients will be tested by ELISA Kit (R&D Systems, Minneapolis, MN, USA). The clinical data will be tested in the point-in-time followed by protocols on the day of enrollment and periodically thereafter until the time of discharge or death, including the numbers of blood products transfusion (including platelets), antibiotics, concomitant medication, days free from advanced organ support, adverse events and the length of ICU or hospital stay. And if several clinical data or measurements will be performed at one day, the lowest/worst data will be retained. Patient status (survive or death) at the 28 days will be recorded through chart review or contact patients if necessary, and the major causes of death will be recorded if the patients will be died. Flowchart of this study procedure can be seen in Fig. 1.

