### Data management and monitor

The data in the study will be managed by clinical trial staffs who will be authorized by the site PI at the sites. The site PI will be responsible for ensuring the accuracy, completeness, legibility, and timeliness of the data reported in the site. Researchers were not permitted to interpret records, and other researchers who are not involved in the patients’ treatment will assess the outcomes. Furthermore, to ensure inter-site reliability, the PIs will explicate operations manual (including the definitions for CRFs and guidelines for collecting data) before data collection and frequent communications among PIs will be kept through e-mail and WeChat during the trial.

Clinical Research Institute of Shanghai Jiao Tong University Medicine School will be responsible for the clinical data management. The Electronic Data Capture (EDC) system will be supplied by Edetek Inc. (Princeton, NJ, USA). All patients’ data will be recorded on paper CRFs and then enter into EDC system. Data in the EDC system will be checked by built-in algorithm, monitored when some modification is required, and traceable to source data. The trial sponsor ([name]. W, Shanghai General Hospital, China) have access to the final trial dataset.

Data and Safety Monitoring Committee (DSMC), independent from the coordinating centers and investigators, will perform an ongoing review of predefined safety parameters and overall study conduct. The DSMC established by Clinical Research Institutes of Shanghai General Hospital and Shanghai Jiao Tong University School of Medicine will be comprised of experts in clinical trials, biostatistics and intensive care medicine.

On all study-specific documents, other than the signed consent, the participant will be referred to by the study code, not by name. All study-specific documents at all centres including source document verification, informed consents, data quality, study drug reconciliation and the table of follow-up will be monitored by DSMC on several occasions during the study, independent from investigators and the sponsor. Besides, the study may also be audited by local or national regulatory authorities.

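### The only general safety outcome counts drug-related events, which controls cannot have, and the serious adverse event definition wrongly requires the event to be unexpected

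*Protocol article*

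**What the plan says.** In the Protocol article, Secondary outcomes, item 8 is "The incidences of drug-related adverse events". It is the only general adverse event outcome among the nine items, and the drug is not named. Study design and setting states: "Patients in control group will not be treated with any platelet-elevating drugs". No placebo is described. Under Blinding: "No blinding will take place in this study". The Objectives include showing that rhTPO is safe as well as effective.

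Study design and setting also gives the safety reporting rule and definition: "Drug-associated serious adverse events should be reported to Shanghai General Hospital within 24 h", and "Serious adverse events are defined as any unexpected medical occurrence that meets one of more of the following criteria". The criteria that follow are death, threat to life, and lasting or significant disability.

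Other sections are wider. Data collection lists "concomitant medication, days free from advanced organ support, adverse events and the length of ICU or hospital stay" for every enrolled patient, with no relatedness limit, up to discharge or death. Data management and monitor says that "other researchers who are not involved in the patients’ treatment will assess the outcomes", and provides an independent committee that reviews predefined safety parameters.

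**The concern.** There are two separate problems.

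First, an outcome restricted to events attributed to a drug that only one arm receives is not a randomised comparison. Its value in the rhTPO arm depends on how often an assessor blames rhTPO instead of sepsis, and in these patients sepsis offers an alternative cause for many events. The Background says that safety of rhTPO in sepsis is still unclear, so a between-arm comparison of harm is what a reader will look for. Thrombosis is the obvious example. The drug raises platelets, and the Background itself links platelets to thrombosis and sepsis to local microthrombosis.

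Second, seriousness describes what happened to the patient, while expectedness describes whether it was foreseeable. Making the second a condition of the first means that a foreseeable life-threatening event is not a serious adverse event in either arm.

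**Working it through.** **Inputs.** The documents give no adverse event rate and no attribution share, so no stated figure on this point can be reproduced. The only number taken from the plan is the arm size of 100 (Sample size). That section reproduces: with 50% vs 30%, two-sided 5% and 80% power, the unpooled formula gives (1.96 + 0.842)² × (0.25 + 0.21) / 0.20² = 90.3, so 91 per arm, and 91 × 1.1 = 100.1. All event rates and attribution shares in steps 2 and 3 are assumptions.

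**Step 1: can a control patient score on item 8?** If the drug means rhTPO, no. The text does not say so, but rhTPO is the only study drug, and the same article speaks of injury directly caused by rhTPO when it covers treatment costs. The control count is then 0 by definition.

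**Step 2: no true harm.** Assume that 20% of patients in each arm have an event, and that a share *a* of the rhTPO-arm events is attributed to the drug. The attributed count is binomial with n = 100 and p = 0.20 × *a*. Against 0 of 100, Fisher's exact two-sided p is 0.059 for 5 events and 0.029 for 6. The chance of 6 or more attributed events is:

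| Attribution share *a* | p | Chance of at least 6 |
|---|---|---|
| 10% | 0.02 | 2% |
| 25% | 0.05 | 38% |
| 50% | 0.10 | 94% |

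If the two counts were tested, the test could therefore look positive with no difference between arms.

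**Step 3: a true excess.** Assume 10% in controls and 20% with rhTPO. The expected count on item 8 is 100 × 0.20 × *a* against 0, that is 0, 2, 5, 10 or 20 events for *a* = 0, 10, 25, 50 or 100%. Counting all events regardless of cause gives about 20 vs 10, the actual contrast. Power for that comparison at 100 per arm (normal approximation, two-sided 5%) would be 51%. It would be 66% for 5% vs 15% and 80% for 10% vs 25%. The all-cause comparison is thus only moderately powered, but it estimates the right quantity.

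**Step 4: the word *unexpected*.** The Sample size section plans for mortality of 30% and 50%. With 100 per arm, that is 30 + 50 = 80 anticipated deaths among 200 patients. In such a population many deaths and life-threatening events are foreseeable, so the literal definition would exclude them from the serious category. The exclusion acts in both arms. The deaths are still counted in the primary outcome; non-fatal life-threatening events have no such backstop. The 24-hour report then applies a second filter, drug association.

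**Step 5: what is covered elsewhere.** All-cause 28-day mortality is the primary outcome. Bleeding, transfusion, organ function markers, days free from organ support and length of stay are secondary outcomes in both arms, with no reference to cause. What remains uncovered is a non-fatal, non-bleeding event that shows up at most indirectly through organ function or support.

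**The case against.** The strongest reply is that the trial does not lose the harms data. Adverse events are recorded for all patients without a relatedness limit, major harms are compared between arms whatever their cause, and causes of death are recorded. The 24-hour rule governs notification, not what is recorded or analysed. The monitoring committee's safety parameters are not listed in the article and may well include all serious events by arm. Stopping is not confined to drug-associated events either, since the management committee or a regulator may request it. No test is specified for item 8, so a descriptive incidence in the treated arm is consistent with the text. The article does not say who judges relatedness, and outcomes are assessed by researchers outside the treating team.

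Most of this stands, and it rules out three stronger readings. A reader might infer that excess harm goes unseen, or that the arms cannot be compared for harm; the outcome list and the data collection section contradict both. A reader might cite organ failure as an uncounted harm, but organ function and support are outcomes in both arms. A reader might also think that the word *unexpected* helps to put controls at zero; it does not, because it narrows serious events in both arms.

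The reply does not rescue item 8 or the definition. Recording an event does not make it an outcome. The non-treating assessors are not said to be masked to allocation. An analysis plan could add all-cause tables, but it would not correct the definition that sites use to classify events as serious.

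**Conclusion.** The point holds in a limited form. As defined, item 8 measures attribution in one arm and is not a between-arm comparison, although safety is part of the objective. This rests on reading the drug as rhTPO, which the context supports but the text does not state. The practical gap is an excess of non-fatal, non-bleeding events, thrombosis being the clearest example, that is ascribed to sepsis. The definition of a serious adverse event is a separate error affecting both arms.

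The primary outcome, its analysis and the sample size are untouched. The illustrations show how item 8 depends on the attribution share; because their rates are assumed, they are not evidence of how large the problem would be. This should be fixed, but it does not threaten the trial's main conclusion.

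**What to change.** - Redefine item 8 as all adverse events and all serious adverse events from randomisation to day 28, compared by arm regardless of attributed cause. Tabulate thromboembolic events by arm. Keep relatedness as a description for the rhTPO arm.
- Delete *unexpected* from the definition of a serious adverse event, and use expectedness only for expedited reporting.
- Include serious adverse events by arm, irrespective of attribution, in what the monitoring committee reviews.

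The cost is small. The changes are to wording in three places, and the case report form already collects adverse events for everyone. There are more events to tabulate. Because collection now ends at discharge or death, patients discharged before day 28 would need adverse event follow-up to that day; the plan already ascertains their survival status then by chart review or contact.

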### Data collection

A case report form (CRF) will be used for all patient who met the enrollment criteria to collect the data. Patients will be followed up to 28 days after randomization. The data will be abstracted from the patients’ electronic medical records: age, ethnicity, gender, patients’ type (medical/surgical), co-comorbidities, sites and pathogens of infection. Then, clinical characteristic baseline and laboratory results were tested within the first 24 h after randomization, including markers of organ functions and biomarkers of infection (Procalcitonin, C-reactive protein, Endotoxin). The severity of disease scores will be recorded, including APACHE II, SOFA, and DIC scores [32] in the first 24 h. The basic serum TPO level in patients will be tested by ELISA Kit (R&D Systems, Minneapolis, MN, USA). The clinical data will be tested in the point-in-time followed by protocols on the day of enrollment and periodically thereafter until the time of discharge or death, including the numbers of blood products transfusion (including platelets), antibiotics, concomitant medication, days free from advanced organ support, adverse events and the length of ICU or hospital stay. And if several clinical data or measurements will be performed at one day, the lowest/worst data will be retained. Patient status (survive or death) at the 28 days will be recorded through chart review or contact patients if necessary, and the major causes of death will be recorded if the patients will be died. Flowchart of this study procedure can be seen in Fig. 1.

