### Randomization

Eligible patients will be randomly assigned to the control and rhTPO add-on treatment in a dynamic random and competitive design in clinical trial sites. Sequential organ failure assessment (SOFA), Acute Physiology and Chronic Health Evaluation II (APACHE II) scores are as the dynamic equilibrium factors. Randomization will be done after the first assessment, ensuring that the assessing occupational therapist will not be biased at this time by knowing the group assignment. A random number will be generated before the start of this study. The random number list will be kept by the third party and uploaded into a random data assigned system. When a patient is recruited in this study, the patient will then be assigned a random number by the system with corresponding treatment. If a patient is later excluded for any reason, the patient’s position in the randomization list will not be replaced by any new patient. Patients will be recruited consecutively. After forty patients have been recruited, the dynamic arithmetic will be introduced. Then, the random number assigned by the system will based on the equilibrium of dynamic factors.

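### Baseline laboratory values may be taken up to 24 h after randomisation, the same window in which rhTPO may start, and it is unclear which SOFA and APACHE II scores are the baseline set

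*Protocol article*

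**What the plan says.** All references are to the protocol article.

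- **Data collection, laboratory values.** "clinical characteristic baseline and laboratory results were tested within the first 24 h after randomization". The sentence goes on to name organ-function markers and the infection biomarkers procalcitonin, CRP and endotoxin.
- **Data collection, severity scores.** "The severity of disease scores will be recorded, including APACHE II, SOFA, and DIC scores [32] in the first 24 h". No start point is given for these 24 h.
- **Data collection, several values on one day.** "if several clinical data or measurements will be performed at one day, the lowest/worst data will be retained". Baseline is not exempted.
- **Study design and setting.** "The time from randomization to administration of rhTPO will be within 24 h". Nothing requires the baseline sample to precede that dose.
- **Randomization.** "Randomization will be done after the first assessment", and SOFA together with "Acute Physiology and Chronic Health Evaluation II (APACHE II) scores are as the dynamic equilibrium factors". The balancing algorithm is not used from the first patient: "After forty patients have been recruited, the dynamic arithmetic will be introduced".
- **Blinding.** The trial is open-label.
- **Secondary outcomes.** Items 4 and 5 are changes in the infection biomarkers and in the organ-function markers.
- **Statistical methods.** 28-day mortality is compared by chi-square. Proportions are also analysed by logistic regression with an unnamed baseline covariate and group as a fixed factor.

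**The concern.** A baseline value serves as a reference because allocation cannot have influenced it. Here the stated laboratory window opens at randomisation and closes 24 h later. Throughout it the treating team knows the allocation, and in one arm the study drug may already have been given. A reference value taken then can carry part of what the change outcome is meant to measure. It can also carry differences in care or in sampling frequency that follow from knowing the arm.

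Three things are at stake. First, the changes in procalcitonin, CRP, endotoxin and organ-function markers may be measured from a contaminated starting point. Second, if such a value is the baseline covariate in the logistic model, the model conditions on something treatment may have altered. Third, the baseline table may describe patients after allocation rather than at entry. The severity scores raise a related question of identity: the scores used to balance the arms and those reported as baseline may be two different sets.

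**Working it through.** No figure in the plan is in dispute, so the check compares the time windows and then asks what follows for each analysis.

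**1. Windows, with randomisation at time 0**

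| Item | Window | Section |
|---|---|---|
| First assessment | before 0 | Randomization |
| SOFA and APACHE II for allocation | before 0, needed once 40 patients are recruited | Randomization |
| Baseline characteristics and laboratory results | 0 to 24 h | Data collection |
| First rhTPO dose | 0 to 24 h | Study design and setting |
| APACHE II, SOFA and DIC scores | 24 h, start not stated | Data collection |
| Serum TPO level | no time stated | Data collection |

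The laboratory window and the dosing window coincide. Let B be the time of the baseline sample and D the time of the first dose. The text permits B > D in the rhTPO arm. In controls there is no D, so a post-dose baseline cannot occur. In both arms B is after allocation.

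**2. Effect on a change outcome**

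Let Δ be the true between-arm difference in change from the value at randomisation. Let δ be the between-arm difference in mean baseline-labelled values that arises after randomisation, from an early drug effect, different open-label care or different sampling. Change is the later value minus the baseline-labelled value, so:

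estimated difference in change = Δ − δ

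With a baseline taken before randomisation, δ is zero in expectation. With the stated window it need not be. If δ has the same sign as Δ, the estimate shrinks; if the opposite sign, it grows. The document gives no value for δ.

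**3. The worst-of-day rule**

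When several measurements fall on one day, "the lowest/worst data will be retained". Applied to the day of enrolment, this can select the baseline value from measurements after randomisation. The number of measurements may differ by arm when care is open-label. The direction is not fixed: in a patient who is improving, the worst value is the earlier one.

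**4. Severity scores**

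Of the planned 200 patients, 200 − 40 = 160 fall under dynamic allocation, so their SOFA and APACHE II must be known before allocation. Data collection does not say whether its 24 h recording refers to those scores or to a later set. The preceding sentence counts from randomisation, which suggests the later reading, but this is an inference from sentence order.

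**5. What is not touched**

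The chi-square test uses only group and 28-day vital status. The sample size uses only 30% versus 50%, two-sided α 0.05 and 80% power. With unpooled variance:

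n = (1.960 + 0.842)² × (0.30 × 0.70 + 0.50 × 0.50) / 0.20² = 7.85 × 0.46 / 0.04 ≈ 90.3, so 91 per group

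This matches the plan. No baseline value enters either.

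**The case against.** The best case for the plan is that its intended order is clear. The Study design section lists assessments at baseline, after the intervention and at 28 days, which treats baseline as preceding treatment. The Randomization section puts a first assessment before allocation. Scoring patients before allocation and entering the scores on the CRF within 24 h can both be true. The article is condensed, its flowchart is not shown, and the Data management section mentions an operations manual with CRF definitions and data-collection guidance. Finally, the logistic covariate is not named and could be the allocation scores.

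Much of this stands. For the scores, the text is ambiguous rather than flatly contradictory. The covariate problem arises only if a value from the post-randomisation window is used. Bias also requires that the value be affected by treatment or by knowledge of the arm. The document gives no evidence that procalcitonin, CRP or endotoxin move within hours of a first dose; its only timing figure for rhTPO, in the Discussion, is platelet recovery within 5 days.

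The core remains. The laboratory window is not a detail left to another document: the article states it, and states it as after randomisation.

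A reader might infer more than the text supports:

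- **Every change outcome is compromised.** Not shown. A platelet count below 50 × 10⁹/L is an entry criterion, so a pre-randomisation count exists for every patient and could serve as the reference.
- **The DIC exclusion is contradicted.** It is not. Confirmed DIC can be excluded at screening and a DIC score still recorded later for severity.
- **The serum TPO sample is post-dose.** No draw time is given. The text leaves this open and does not establish it.
- **A definite share of rhTPO patients has a post-dose baseline.** The document gives no distribution of sampling or dosing times. The share could lie anywhere from 0% to 100%, and it would not measure bias in any case.

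**Conclusion.** The point holds, with moderate weight. As written, baseline laboratory values can be post-allocation in both arms and post-dose in the rhTPO arm only. This can bias secondary outcomes 4 and 5, and any logistic model that takes such a value as its covariate. The article also leaves unclear whether the baseline SOFA and APACHE II are the scores used for allocation.

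The size of the bias cannot be stated. It depends on actual sampling and dosing times, on how fast the markers respond and on how open-label care differs, none of which the document gives. If every sample were in practice drawn before the first dose, the drug could not have altered it, and only the influence of known allocation would remain.

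It would be wrong to infer that the primary result is at risk. The unadjusted chi-square comparison of 28-day mortality uses no baseline value, and the sample size stands as calculated. A logistic model for mortality would be exposed only if its covariate came from the post-randomisation window.

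**What to change.** Reconcile the Study design, Randomization and Data collection sections as follows:

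1. Define baseline as the last value before randomisation, within the preceding 24 h, for platelets, laboratory values and infection biomarkers.
2. Exempt baseline from the worst-of-day rule, and apply that rule only to values after randomisation.
3. Use the pre-randomisation SOFA and APACHE II, as entered for allocation, as the baseline scores and as the covariates.
4. State that the basic serum TPO sample is drawn before the first rhTPO dose.
5. Label any value taken after randomisation as Day 1, not baseline.

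The cost is slightly earlier blood sampling and changed protocol and CRF wording. No tests are added. The change is best made before recruitment or as early in it as possible, because a missed pre-dose sample cannot be recovered.
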